## **7.7 Blood Collection**

Up to 20 mL of blood will be collected at the Screening Visit and up to 70 mL of blood will be collected at each later visit, usually from the antecubital fossa, according to the Schedule of Procedures (Appendix A1). Less blood may be collected if lab results can be obtained from specimens collected on the same date for the Open B study.

All specimens will be handled according to the procedures specified in the Study Operations Manual.

In the event of an abnormal laboratory value, volunteers may be asked to have an additional sample collected at the discretion of the principal investigator or designee.

## **7.8 Urine Collection**

Up to 50 mL of urine will be collected at the specified timepoints in the Schedule of Procedures (Appendix A1). All specimens will be handled according to the procedures specified in the Study Operations Manual. In the event of an abnormal laboratory value, volunteers may be asked to have an additional sample collected at the discretion of the principal investigator or designee.

## **7.9 Swab Collection of mucosal secretions**

Swabs collecting mucosal secretions (to determine antibody secretion) will be used by the volunteers, after instruction, at the screening visit (see Section 7.2.). All specimens will be handled according to the procedures specified in the Study Operations Manual. In the event of an abnormal laboratory value, volunteers

may be asked to have an additional sample collected at the discretion of the principal investigator or designee.

#### **7.10 Hair Collection**

Hair samples will be collected from volunteers at the specified time points in the Schedule of Procedures (Appendix A1). Details on hair collection are provided in the Study Operations Manual.

#### **7.11 Reimbursement**

Volunteers will be reimbursed for their time, effort and for costs to cover their travel expenses to the study research centre and any inconvenience due to study participation. Reimbursement will be made after the completion of each study visit. Research centre specific reimbursement amounts will be documented in the research centre-specific Volunteer Information Sheet approved by the Ethics Committee.

#### **7.12 Randomization and Blinding**

Volunteers will be identified by a unique volunteer identification number.

The randomization schedule(s) will be prepared by the statisticians at the Data Coordinating Center (DCC) prior to the start of the study. Volunteers will be assigned a specific allocation number. An unblinding list will be provided to the research centre by the DCC for use in case of medical emergency as described below.

This study is double-blinded. Research centre personnel (investigator and clinical personnel monitoring the safety and laboratory assay results) and volunteers will be blinded with respect to the allocation of investigational product (placebo or FTC/TDF) but dosing regimen, daily or intermittent, will not be blinded.

Volunteers will be informed about their group assignment once the database is locked. If a study volunteer is unblinded and becomes aware of treatment group assignment, further administration of the investigational product (FTC/TDF or placebo) will be discontinued. The study volunteer will be followed up until the end of the study.

#### **7.13 Unblinding Procedure for Individual Volunteers**

Unblinding of an individual volunteer may be indicated in the event of a medical emergency when the clinical management/medical treatment of the volunteer would be altered by knowledge of the group assignment.

The unblinded information should be restricted to only a small group of individuals involved in clinical management/medical treatment of the volunteer (e.g., treating physician) and the blind should be maintained for those responsible for the study assessments.

The reasons for unblinding should be documented and the IAVI Medical Monitor and the Data Coordinating Centre should be notified. The procedures and contact numbers for unblinding are outlined in the Study Operations Manual.

## 8.0 INVESTIGATIONAL PRODUCT

### 8.1 Description

This study evaluates the use of FTC/TDF (FTC 200mg /tenofovir disoproxil fumarate 300mgFTC co formulation) or placebo. The placebo will appear identical to FTC/TDF.

FTC/TDF tablets are fixed dose combination tablets containing 200 mg FTC and 300 mg TDF disoproxil fumarate as active ingredients.

FTC is a nucleoside reverse transcriptase inhibitor (NRTI) approved as once-a-day capsule (200 mg) in combination with other antiretroviral agents, for the treatment of HIV-1 infection. FTC is a synthetic analogue of the naturally occurring pyrimidine nucleoside, 2'-deoxy cytidine. Intracellularly, FTC is phosphorylated by cellular enzymes to form FTC triphosphate, the active metabolite. Tenofovir disoproxil fumarate (Viread, also known as TDF) the oral prodrug of tenofovir, is a nucleotide reverse transcriptase inhibitor (NRTI) approved as a once-a-day tablet (300 mg), in combination with other antiretroviral agents, for the treatment of HIV-1 infection. After absorption, tenofovir DF is rapidly converted to tenofovir, which is metabolized intracellularly to the active metabolite, tenofovir diphosphate (PMPApp).

FTC/TDF tablets are for oral administration. Each blue, film-coated, capsule-shaped tablet is labelled with 'GILEAD' on one side. Each tablet contains 200 mg of FTC and 300 mg of TDF (which is equivalent to 245 mg of tenofovir disoproxil), as active ingredients. The tablets also include the following inactive ingredients: croscarmellose sodium, lactose monohydrate, magnesium stearate, microcrystalline cellulose, and pregelatinized starch (gluten free). The tablets are coated with Opadry II Blue Y-30-10701, which contains FD&C Blue #3 aluminium lake, hypromellose, lactose monohydrate, titanium dioxide, and triacetin.

The placebo tablets match the FTC/TDF tablets in appearance. Each tablet contains the following inactive ingredients: microcrystalline cellulose, croscarmellose sodium, pregelatinized starch, lactose monohydrate, and magnesium stearate. The tablets are film-coated with FD&C Blue #2 aluminium lake, hypromellose, lactose monohydrate, titanium dioxide, and triacetin.

See the Investigators Brochure for details of the chemical structure and properties of both drugs.

### 8.2 Shipment and Storage

Authorization to ship the investigational product to the research centre will be provided in writing by the sponsor (IAVI), upon confirmation that all required critical documents for shipment authorization are completed. The investigational product will be shipped to the research centres at 25 °C and stored there at 25 °C. Temperature excursions will be allowed between 15-30 °C.

### **8.3 Dispensing and Handling**

The investigational product will be dispensed as specified in the Study Operations Manual. Designated research centre personnel will ensure that the allocation number matches the allocation number assigned to the volunteer. The investigational product will be used as supplied by the manufacturers with no further preparation.

Daily dosing: 1 tablet orally daily

Intermittent dosing: 1 tablet orally Monday and Friday and again within 2 hours after sexual intercourse (except on Monday and Friday), not to exceed 1 dose per day.

Study volunteers will be instructed to store investigational product below 40 °C.

### **8.4 Distribution**

Investigational product will be distributed according to the Schedule of Procedures (Appendix A1).

Investigational product will be distributed approximately every 4 weeks in a pill bottle fitted with a MEMS TrackCap. Volunteers will receive sufficient pills to allow for the daily or intermittent regime i.e., twice weekly doses, post-coital doses up to one total dose per day (except on the days of the weekly doses, Monday and Friday) for the 4 weeks between study visits. Unused pills will be accounted and collected at the next visit prior to dispensation of the next month's supply.

Further information on the distribution of the investigational product is supplied in the Study Operations Manual.

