### **6.3 Post-randomization Visits for HIV-uninfected volunteers**

The volunteer will be asked to return to the clinic on the days specified in Appendix A1. Procedures will be conducted at these visits as specified in Appendix A1.

During these visits, routine safety laboratory parameters from the previous visit will be reviewed. If a volunteer had an abnormal laboratory value, specified guidelines (Section 12.0) will be followed.

HIV pre-test counselling will be conducted if an HIV test is required (Appendix A1) and post-test counselling will be provided if the results of a prior HIV test are given to the volunteer.

At the Week 4 visit only, a single-dose timed pharmacokinetic study will be conducted. In addition to the procedures listed above, the following procedures will be conducted:

- To reduce the variability in test results, volunteers will be asked to eat a standard meal
- After eating, collection of blood specimen for plasma and intracellular drug levels
- Witnessed dosing of investigational product immediately after specimen collection
- Repeat collection of blood specimen approximately 2 hours after dosing
- Repeat collection of blood specimen approximately 24 hours after dosing

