### 9.4. Adherence Assessments

Adherence to and dosing of investigational product will be assessed through MEMS data, follow-back interview and plasma/intracellular drug levels at the time points indicated in Appendix A1.

*MEMS electronic medication-monitoring pill bottle caps.* Daily medication adherence data will be collected using the AARDEX Medication Event Monitoring System (slightly larger than a standard pharmacy-sized bottle cap with an electronic chip that clocks bottle openings in a 24-hour period). This measure provides complete information on patterns of adherence, including treatment interruptions. Each volunteer will be assigned a MEMS TrackCap to be used on his or her study drug pill bottles. MEMS data for all volunteers regardless of assignment group will be uploaded from the device at monthly visits as indicated in Appendix A1.

*Self-reported adherence.* At timepoints indicated in the Schedule of Procedures (Appendix A1) self-reported adherence to PrEP will be collected using a follow-back interview which is a structured self-report of number of doses missed. A 30 day self-report was shown to be closely associated with MEMS adherence in Uganda [77,110].

*Plasma drug levels.* Plasma from all volunteers will be stored at multiple visits as indicated in Appendix A1 for retrospective assessment of drug plasma levels in those volunteers assigned to FTC/TDF. The plasma half-life of tenofovir after a single oral dose is approximately 17 hours, but drug remains detectable (>10ng/mL) out to 48 hours [43]. At the end of the study after treatment assignment has been unblinded, samples will be selected from up to 4 visits when the volunteer's MEMS data indicate dosing with FTC/TDF within 48 hours of the visit and tested for plasma drug levels.

Two additional adherence measurements will be explored. Intracellular drug levels will be measured in volunteers assigned to FTC/TDF. PBMCs will be collected from all volunteers at the time points indicated in Appendix A1. After

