#### **14.2.4 Adherence**

The mean, median and range of adherence to PrEP will be determined using MEMS data for volunteers. Previous work has shown that the accuracy of MEMS assessment can be improved with a 3-day structured self-report of the number of extra cap openings and the number of times multiple doses are taken out of the bottle [119]. The *adjusted MEMS adherence* is calculated by the interview adjusted number of bottle openings/number of doses prescribed over the prior three days. The *unadjusted MEMS* measure is the number of electronically recorded bottle openings divided by the number of expected doses based on IVR sexual activity data, since the last interview[48]. MEMS adherence will be classified by the schema proposed by Vrijens where adherence is organized in terms of persistence and execution [161,162]. Persistence is time to treatment discontinuation. Treatment discontinuation will be defined as the first day of 30 consecutive days without a MEMS cap event. Treatment execution is defined as the number of MEMS caps events divided by the number of expected doses prior to treatment discontinuation. We also will use MEMS to characterize treatment interruptions and whether patterns of adherence are temporally related to sexual behavior. These approaches have been successfully piloted in Uganda [77,94].

For volunteers assigned to intermittent regimens, a combination of MEMS and IVR/SMS data will be used. Each day will be classified as an adherent or nonadherent day. Adherent days will be defined as: any day on which sexual activity was reported and a MEMS event occurred, any Monday or Friday on which a MEMS event occurred, and any other day of the week on which neither sexual activity nor a MEMS event occurred. Adherence will be calculated as the number of adherent days since the last visit divided by the number of days since the last visit.

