We will examine the degree of correspondence between MEMS and 30 day recall data using a linear model, taking repeated measures into account, to compare predicted adherence from MEMS and IVR/SMS with 30 day recall data. Similarly adherence from MEMS will be compared with plasma and intracellular drug levels for correspondence. We will determine if PrEP adherence declines over time by comparing median adherence each month using a linear model, testing for a non-zero slope and proportion >90% adherent using logistic regression. Finally we will describe time to PrEP discontinuation (or non-persistence), defined by >30 days without a MEMS event, with Kaplan-Meier methods. Volunteers who discontinued study treatment due to intolerance, toxicity, or pregnancy will be censored at the time of treatment discontinuation.

With 24 volunteers per treatment group, a two-sided, 0.05 level binomial test of 75% adherence will have only 29% power to detect a true adherence rate of 90%. Power increases to 66% if the true adherence rate is 95%.

If we combine the intermittent FTC/TDF and intermittent placebo groups (n=36), then a two-sided, 0.05 level binomial test of 75% adherence will have 51% power to detect a true adherence rate of 90%. Power increases to 90% if the true adherence rate is 95%. Likewise, if we combine the daily FTC/TDF and the daily placebo groups (n=36), we will have reasonable power to detect high rates of adherence.

The relationship between adherence and intracellular drug level will be evaluated in the volunteers assigned to active regimens FTC/TDF. Determining the relationship between adherence and intracellular drug levels may provide adherence estimates for future studies which do not include detailed objective adherence measures. The correlation between mean adherence execution over the prior month and intracellular drug level will be tested using Pearson's correlation coefficient. Mean drug levels in individuals with  $\geq 90\%$  adherence will be compared with those with <90% adherence using a student's T test.

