| Drug accountability (pill count/unused pills)                                                                                                                                                                                                        |        |       |     |     | X     |            | X      | X     | X         |       |             |           |           |
| Upload MEMS data                                                                                                                                                                                                                                     |        |       |     |     | X     |            | X      | X     | X         |       |             |           |           |
| Consent / Counselling / Assessments / Questionnaires                                                                                                                                                                                                 |        |       |     |     |       |            |        |       |           |       |             |           |           |
| Informed Consent and assessment of understanding                                                                                                                                                                                                     | X      |       |     |     |       |            |        |       |           |       |             |           |           |
| Screening Questionnaire                                                                                                                                                                                                                              | X      |       |     |     |       |            |        |       |           |       |             |           |           |
| HIV risk Assessment                                                                                                                                                                                                                                  |        | X     |     |     |       |            |        |       |           |       |             |           |           |

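### Unless clinic openings of the capped bottle are excluded, the 30-day MEMS rule for stopping is longer than the 28-day supply cycle and misses stops by volunteers who keep attending

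*Protocol*

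**What the plan says.** Section 14.2.4 splits MEMS adherence into persistence (time to discontinuation) and execution (cap events over expected doses before discontinuation). The stopping rule reads: "Treatment discontinuation will be defined as the first day of 30 consecutive days without a MEMS cap event". Later in the same section the Kaplan-Meier analysis uses a slightly different rule: "defined by >30 days without a MEMS event, with Kaplan-Meier methods".

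Section 3.3.3.1 says the cap stores the date and time of each opening, and concedes that an opening is not a dose.

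Three places describe how the bottle is handled:
- Section 8.4: "Investigational product will be distributed approximately every 4 weeks in a pill bottle fitted with a MEMS TrackCap", and "Unused pills will be accounted and collected at the next visit prior to dispensation of the next" month's supply.
- Section 9.4: "Each volunteer will be assigned a MEMS TrackCap to be used on his or her study drug pill bottles".
- Appendix A1: the row "Drug accountability (pill count/unused pills") is marked at W4, W8, W12 and W16, and product provision at W0, W4, W8 and W12.

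The only correction offered for openings that are not doses (Sections 3.3.3.1 and 14.2.4) relies on the volunteer's own report and feeds an adherence ratio over three days. It does not enter the persistence definition. No section mentions openings made by staff or at the clinic.

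**The concern.** Counting and collecting the contents of a bottle, and putting one assigned cap on successive bottles, can hardly be done with the bottle closed. If so, the trial itself creates a cap event about every 28 days, while its rule for stopping needs 30 days without one. For a volunteer who stops taking pills but keeps coming with the bottle, the rule then responds to the spacing of clinic visits and not to pill-taking.

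Three results would be distorted. The Kaplan-Meier curve would show too few stops. A stop that is detected could be dated to the day after a clinic visit instead of the day it happened. A stop that is missed would stay in the execution denominator, so non-persistence would be reported as poor execution and the split that Section 14.2.4 sets up would be lost.

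**Working it through.** The plan gives no figure to reproduce, so this is a day count from its own rule and schedule.

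**Inputs.** Threshold: 30 event-free days, or more than 30 (Section 14.2.4). Nominal visits: days 0, 28, 56, 84 and 112. Windows: -7/+2 days at W4, W8, W12 and W16 (Appendix A1). Event-free days between two clinic openings = visit gap minus 1, counted from the day after the earlier visit.

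1. **Visits exactly on schedule.** Every gap is 28 days, so the longest run is 28 - 1 = 27 days. The rule is not met, whenever the volunteer stopped.

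2. **W0-W4 at the window limits.** W4 falls on days 21 to 30, so the longest run is 30 - 1 = 29 days. This interval can never qualify.

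3. **Later intervals at the window limits.** The gap runs from 28 - 7 - 2 = 19 to 28 + 2 + 7 = 37 days, so the run is 18 to 36 days. Thirty event-free days need a gap of at least 31 days, that is, a later offset exceeding the earlier one by at least 3.

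4. **How often a later interval qualifies.** Assume each of the 10 days in a window is equally likely and visits are independent. The plan does not state this; it is for illustration. Offset differences of 3 to 9 arise in 7+6+5+4+3+2+1 = 28 of 100 pairs, or 28%. For more than 30 days the difference must be at least 4: 21 of 100, or 21%.

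5. **At least one qualifying interval, 30-day rule**, by the number of complete later intervals left after the stop:
   - one: 28%;
   - two: 0.28 + 0.28 - 0.02 = 54%, where 0.02 is the chance that both adjacent intervals qualify (20 of 1,000 triples);
   - three: 0.84 - 0.02 - 0.02 - 0.0784 + 0.0001 = 72%.

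6. **With clinic openings removed.** If the cap is collected on day 112, a last own opening on or before day 112 - 31 = 81 meets the 30-day rule.

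7. **Effect on persistence (illustrative).** Suppose 6 of 36 volunteers on one regimen stop and keep attending. True persistence is 30/36 = 83%. With exact 28-day visits, 100% is reported. At the detection rates in step 5, about 4.3, 3.2 or 1.7 of the 6 are found, so about 88%, 91% or 95% is reported.

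8. **Effect on execution (illustrative).** A daily volunteer takes every dose to day 28, stops, and attends on schedule. Execution before the stop is 28/28 = 100%, with persistence of 28 days. With clinic openings counted, one per visit day, the volunteer is never classed as stopped, and execution is (28 + 3)/112 = 28%.

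9. **Effect on the other measures.** One clinic event on each of four visit days is 4/112 = 3.6 points at most, for daily openings over expected doses or for the intermittent adherent-day rule.

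**The case against.** The strongest reply is that the premise is inferred. No section says that staff open the capped bottle or that such openings stay in the data. Sections 8.3 and 8.4 leave handling detail to the Study Operations Manual, and Section 13.3 announces a separate analysis plan; either may remove clinic events. That stands as a limit on certainty. It does not repair the rule, because the protocol itself fixes the event, the threshold and the 4-week cycle, and these do not fit together as written.

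The damage is also largely recoverable. Cap events are time-stamped, visit dates are source data (Section 13.1), and dispensing and return logs are kept (Section 8.5). This is correct, and it is why the fix is cheap.

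The group affected is narrow: volunteers who stop without being taken off product, attend, and bring the bottle. Stops for intolerance, toxicity or pregnancy are censored (Section 14.2.4). Pill counts and interviews at follow-up visits (Section 7.6) would often reveal the others. This stands too.

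A reader might infer that an attending volunteer can never be classed as stopped. The windows contradict that: after W4, in-window gaps reach 37 days. A reader might also infer that the primary adherence endpoint is compromised. Section 5.1.1 uses the proportion taking at least 80% of expected doses, and an early stopper falls below 80% whether or not the persistence rule fires: in step 8, 31/112 is far under it.

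Nor does Section 6.3, which requires "Witnessed dosing of investigational product immediately after specimen collection" at W4, say that the dose comes from the capped bottle. The argument does not need it.

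**Conclusion.** The point holds in a limited form. Unless clinic openings are excluded, the 30-day rule cannot detect a stop by a volunteer attending with the bottle at exact 28-day intervals, nor within W0-W4. In later intervals it works only when two visits happen to be at least 31 days apart: about 28% of intervals under uniform, independent visit days, or 21% under the more-than-30-days wording.

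Descriptive persistence is overstated, detected stops may be misdated, and missed stops are reported as poor execution. No power statement uses persistence. The effect on the 80% endpoint and on the intermittent day rule is small, with the 3.6 points as a ceiling. The conclusion rests on the inference that counting and re-supplying open the cap, and on the absence of an exclusion in documents not shown. It should be corrected, but it does not threaten the trial's main results.

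**What to change.** In Sections 14.2.3 and 14.2.4, state that cap events from clinic handling are removed before days of use, execution, adherent days and time to discontinuation are computed. These are the pill count, the refill and, if taken from the capped bottle, the witnessed W4 dose. Identify them from visit dates and cap timestamps, and have staff note handling times on the dispensing log already required by Section 8.5, so that a volunteer's own opening on a visit day is not deleted with them. Use one threshold, either 30 days or more than 30, in both places in Section 14.2.4.

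The cost is a sentence or two in the analysis section, one entry on an existing log and a small recording burden for staff. It is best settled before enrolment, since unlogged clinic openings may be hard to tell from a volunteer's own on the same day.
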